## Assessment of study parameters

### I. Oswestry disability index (ODI)

Disability related to sLSS will be assessed with the ODI, which is considered the gold standard of low back functional outcome tools [26]. The ODI is a questionnaire comprising 10 self-administered items that quantify a patient's perceived level of functional disability. Each of the items relates to a different area of functional impairment and consists of six statements, which are scored from zero to five points. Patients choose the statement that suits their subjective perception best. In this study, the validated German version of the ODI [27] will be used.

### II. Dynamic compensation

Dynamic compensation is defined as the difference between static and dynamic sagittal spinal alignment. Six possible gait events are available to choose from for the definition of dynamic sagittal spinal balance (left and right; heel-strike, toe-off, midstance). Dynamic sagittal spinal balance may be defined as sagittal spinal balance during left/right midstance, left/right heel strike and/or left/right toe off. Depending on the research question, we will adapt the workflow and use the most appropriate gait event to calculate dynamic sagittal spinal balance.

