#### Primary hypothesis

Hypothesis 1: PROMs correlate with dynamic compensation (difference between static and dynamic sagittal spinal alignment) in patients with sLSS.

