Participants will complete forward-bending, pick-up, trunk torsion, sitting and walking assessments before and after a fatigue exercise. Paraspinal muscle fatigue will be elicited by a modified Biering-Sørensen test [23] on a Roman chair (45° chair inclination, trunk horizontal). The modified Biering-Sørensen test will be conducted immediately before the movement assessments will be repeated to obtain data in the fatigued state. At the very end of the movement analysis, patients will complete the sock test from the back performance scale assessment again with the retroreflective markers attached (approximate duration: 30 minutes).

After the functional biomechanical analysis, radiological data (MRI and EOS) will be collected. MR imaging of the lumbar and abdomen region will be performed using a 0.55T MAGNETOM Free.max scanner (Siemens Healthcare, Erlangen, Germany) with the patients in supine position with extended legs. MR imaging allows the classification of level and severity of stenosis. Patients' back surfaces and markers will be digitized using the contactless optical scanner Artec EVA [24]. This procedure will be performed in the laboratory facilities at the University Hospital of Basel, same as in the previous study approved by the EKNZ (Project ID: 2020-02496 dated 11/12/2020). This procedure does not require any additional preparation of the participant, but their pose will be referenced with a pose frame replicating the standing posture from the EOS radiography (approximate duration: 5–7 minutes). Multi-echo gradient echo (VIBE Dixon) axial images will be acquired for the analysis of the abdominal and paraspinal muscles. A T2-weighted axial image will be selected at each vertebral body level in the center of the body itself identified on the sagittal view image. All sequences are not enhanced (approximate duration: 30 minutes). Finally, upright standing sagittal plane EOS images of the full body including entire spine and pelvis will be captured (approximate duration: 10 minutes). The total duration of the baseline study visit on test day 1 including travel times between facilities will be approximately 3.5 hours. Because baseline and 1-year follow-up entail the same study procedures, a complete study participation will take approximately 7 hours.

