### III. Sagittal spinal balance and spinal loads assessed using motion capture

The curvature of the lumbar and thoracic spine during stance and during walking will be computed from the marker data using MATLAB™ (R2021b, The Mathworks Inc., Massachusetts, USA) software. A cubic polynomial function will be fitted to the marker positions in each time frame, approximating an S-shaped spine curvature with thoracic kyphosis (TK) and lumbar lordosis (LL) curves [1]. The workflow used to calculate sagittal spinal balance parameters is based on the calculation methods for radiological sagittal spinal balance parameters and was established and tested in a previously conducted pilot study (EKNZ Project ID 2021-02012). The set of marker-based sagittal spinal balance parameters comprises LL, TK, sagittal vertical axis (SVA), spino-sacral angle (SSA), spine inclination (SI) (Figure 3).

[figure not shown]

**Figure 3:** Computed Marker Data and Calculation of Sagittal Spinal Balance Parameters [1]

The data obtained using motion capture will be used to estimate spinal load using musculoskeletal modeling [28].

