## 4 STATISTICS AND METHODOLOGY

### 4.1 Sample size calculation

To determine if PROMs correlate with dynamic compensation considering categorical covariates with 3 levels of the covariate a sample size of 111 (37 within each level) is required to detect a correlation of 0.3 at 80% power and 5% significance level. Considering a 10% drop-out rate, 122 subjects will be enrolled in the study.

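### The protocol leaves the primary variable, dynamic compensation, open to later adaptation, so the 5% level of the primary test is not protected

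*Protocol*

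**What the plan says.** - Protocol 2.1 states one primary hypothesis: "PROMs correlate with dynamic compensation (difference between static and dynamic sagittal spinal alignment) in patients with sLSS". Section 2.2 lists two primary endpoints, ODI and dynamic compensation. The other questionnaires appear there under other parameters.
- Protocol 3.3 II defines dynamic compensation as a static-minus-dynamic difference and leaves the dynamic part open: "Six possible gait events are available to choose from" (heel strike, midstance and toe-off, left and right). Combinations of events are allowed. The rule for choosing is: "Depending on the research question, we will adapt the workflow and use the most appropriate gait event to calculate dynamic sagittal spinal balance".
- Protocol 3.3 III gives five marker-based parameters: LL, TK, SVA, SSA and SI. No section says on which of them the difference is taken.
- Protocol 3.3 (study procedures) has patients complete "walking assessments before and after a fatigue exercise". Hypothesis 1 names neither the fatigue state nor the visit.
- Protocol 4.1 says that the sample size "is required to detect a correlation of 0.3 at 80% power and 5% significance level". Section 4.2 plans correlation analysis and gives neither a time by which the definition must be fixed nor a multiplicity adjustment.

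**The concern.** A primary endpoint should be a single quantity, fixed before its association with the outcome is examined. Here the text does more than omit a detail: it gives written permission to adapt the primary variable, under a criterion (most appropriate) that can be applied at any time. The primary research question is already stated in 2.1, so the event for that question could have been named.

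Six events times five parameters give 30 single-event definitions against ODI, before combinations of events, fatigue state or visit are counted. Any of them could be reported as the primary result at 5% without departing from the protocol. At stake is whether a significant primary correlation can be taken at face value. A reader could not tell a definition chosen on biomechanical grounds from one chosen because it correlated.

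**Working it through.** **Inputs from the protocol.** Correlation 0.3, 5% level, 80% power and 111 evaluable patients (4.1); six gait events (3.3 II); five parameters (3.3 III); ODI as the primary questionnaire (2.2). Two-sided testing is assumed, because 4.1 does not state sidedness.

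**Step 1: the plan's own figure.** Fisher z for one correlation:

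n = ((1.960 + 0.842) / atanh 0.3)² + 3 = (2.802 / 0.3095)² + 3 = 84.9, so 85.

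Allowing for the three-level covariate gives 87 (partial correlation, two dummies) or 91 (pooled over three strata). The stated 111 is not reproduced. It equals the total for a three-group ANOVA with Cohen's f = 0.3 (37 per group, power 80.3%), but the protocol does not say that this was used. That is a separate matter. Here it matters only that 111 is more than one correlation needs:

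power = Φ(0.3095 × √108 − 1.960) = Φ(1.257) = 90%, or 88% when pooled over three strata.

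**Step 2: error rate if the best definition is picked.** With independent tests the chance of at least one p < 0.05 under no association is 1 − 0.95^k:
- k = 6: 26.5%
- k = 30: 78.5%

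The definitions are not independent, because all six events subtract the same standing value and the parameters share anatomy. These figures are therefore upper bounds. Correlated candidates were simulated under no association with ODI, with n = 111 and the largest |r| compared with the two-sided 5% critical value of 0.187 (6,000 runs per cell). The protocol gives no correlations, so those in the table are assumptions.

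| Correlation between events | Best of 6 events, one parameter | Best of 30, parameter correlation 0.3 | 0.5 | 0.7 |
|---|---|---|---|---|
| 0.80 | 14% | 50% | 44% | 37% |
| 0.90 | 11% | 40% | 36% | 28% |
| 0.95 | 8–9% | 34% | 31% | 25% |

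One definition fixed in advance gave 4.95%, as it should. Repeat runs moved single cells by about a percentage point, so the ranges are stated as 8–14% and 24–50%. Combinations of events and the fatigue state are not in these counts and would add to them.

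**Step 3: cost of keeping the candidates and adjusting.** Same formula with α = 0.05/k:

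| Tests kept | α | Evaluable n for 80% power | Power at n = 111 |
|---|---|---|---|
| 1 | 0.05 | 85 | 90% |
| 5 | 0.01 | 125 | 74% |
| 6 | 0.0083 | 130 | 72% |
| 30 | 0.00167 | 169 | 53% |

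For five tests: Φ(3.217 − 2.576) = Φ(0.641) = 74%.

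**The case against.** **The choice is tied to the question, not to results.** This stands. A reader might infer that the sponsor will choose after seeing the correlations, so that the 5% level is already lost. The documents do not support that. If one definition is fixed on biomechanical grounds before any association with ODI is examined, the level holds.

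**ODI is the only primary questionnaire.** This also stands. Hypothesis 1 and 4.1 say PROMs and five questionnaires are collected, so a reader might multiply the 30 definitions by five. The endpoint list in 2.2 limits the primary questionnaire to ODI. The plural is a mismatch to reconcile, not a further set of primary tests.

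**Static alignment also exists from EOS and the surface scan.** A reader might fear a difference taken across methods. However, the movement-data part of 3.3 describes the static standing capture, and 3.3 III computes curvature in stance and in walking from markers. EOS and the surface scan are separate secondary endpoints. A constant offset between methods would in any case leave a correlation unchanged.

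**An analysis plan may settle the parameter and the fatigue state.** This is partly right. Silence on those two would be a weak point by itself, and the written rule alone supports only the 8–14% range. But the rule expressly leaves a primary endpoint adaptable, and an analysis plan written late would comply with it.

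**The study is observational and seeks understanding.** True, but it states a primary hypothesis and sizes it at a 5% level, so that level should mean what it says.

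**Conclusion.** The point holds in a conditional form: the 5% level of the primary test is not protected. If the most favourable definition were picked, the false-positive rate would be about 8–14% for event choice alone and about 24–50% if the parameter is open as well, with ODI as the only outcome. Both ranges rest on n = 111, two-sided tests, and assumed correlations of 0.8–0.95 between events and 0.3–0.7 between parameters. The counts of six events and five parameters are exact. Even the mildest case examined exceeds 5%. Power is no obstacle to a remedy: one fixed test keeps about 90% power for a correlation of 0.3 at 111 evaluable patients.

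**What to change.** In 2.1, 2.2, 3.3 II and 4.1–4.2, define one primary test before any correlation with ODI is run:

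- baseline ODI against the standing-to-walking difference of one named marker-based parameter;
- both parts of the difference from marker data;
- recorded before the fatigue exercise;
- at one named gait event, averaged over left and right.

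Which parameter and which event is the sponsor's choice. In Hypothesis 1 and 4.1, replace PROMs by ODI to match the endpoint list. Label all other events, parameters, questionnaires and the post-fatigue state secondary, and limit the adapt-the-workflow sentence to those secondary analyses.

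The cost is protocol wording; no additional data or patients are needed. The downside is that the other variants lose primary status. If all five parameters must stay primary at the one event, Holm adjustment would control the error rate, but power at its strictest step (α = 0.01) falls from about 90% to about 74%. Naming one parameter is therefore preferable.

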### III. Sagittal spinal balance and spinal loads assessed using motion capture

The curvature of the lumbar and thoracic spine during stance and during walking will be computed from the marker data using MATLAB™ (R2021b, The Mathworks Inc., Massachusetts, USA) software. A cubic polynomial function will be fitted to the marker positions in each time frame, approximating an S-shaped spine curvature with thoracic kyphosis (TK) and lumbar lordosis (LL) curves [1]. The workflow used to calculate sagittal spinal balance parameters is based on the calculation methods for radiological sagittal spinal balance parameters and was established and tested in a previously conducted pilot study (EKNZ Project ID 2021-02012). The set of marker-based sagittal spinal balance parameters comprises LL, TK, sagittal vertical axis (SVA), spino-sacral angle (SSA), spine inclination (SI) (Figure 3).

[figure not shown]

**Figure 3:** Computed Marker Data and Calculation of Sagittal Spinal Balance Parameters [1]

The data obtained using motion capture will be used to estimate spinal load using musculoskeletal modeling [28].

### IV. Sagittal Spinal Balance assessed using EOS

Sagittal spinal balance parameters from EOS radiological images are calculated semi-automatically using the sterEOS software provided by the EOS company. Trained radiology technicians follow a workflow during which anatomical landmarks, e.g., the center of a specific vertebra, are marked in the EOS software. Once all required landmarks are marked, the parameters are calculated automatically by the sterEOS software.

This workflow allows the calculation of four sagittal spinal balance parameters: SVA (Figure 4A), SSA (Figure 4A) LL (Figure 4B) and TK (Figure 4B) [29]. LL is calculated as the angle between the tangents on the superior L1 and inferior L5 vertebral endplates. Likewise, TK is calculated as the angle between the tangents on the superior T4 and inferior T12 vertebral endplates. SVA is measured as the horizontal distance between C7 plumb line and the posterior-superior corner of the S1 vertebra. SSA is defined as the angle between the line connecting the center of the C7 vertebra to the center of the S1 endplate and the line parallel to the superior S1 endplate. As a quality control measure, all images are double rated. If two ratings are apart more than five degrees, a third radiological technician rates the images. The final report, which will be used for the analysis, is sent to the patient archive system of the University Hospital Basel.

[figure not shown]

**Figure 4:** Overview of Spinopelvic Sagittal Alignment Parameters (modified from Völlner and Grifka [2])

## V. Sagittal spinal alignment assessed using the optically captured 3D back surface (Artec EVA)

Artec EVA is a CE-approved optical device used in many human studies for digital reconstruction of surface topography (Artec Europe S à r.L. [name]). The device does not come into contact with the patient, and the scanning process is radiation-free and fast. This scanner creates a 3D CAD surface model which can be evaluated directly on a computer screen and requires no additional preparation of the patient (Figure 5).

Topography analysis of the surface can reveal asymmetries of the back shape and underlying structures, but also allow calculation of various external postural parameters such as sagittal spinal balance and trunk inclination, as well as kyphotic, lordotic and cervical angles of the back. Recent advances in the study of spinal deformities with noninvasive technologies showed a promising result for mild to moderate cases [30].

The use of such technology in this study may lead to important conclusions about the status of the external shape and postures of patients with sLSS, comparable to standard EOS images. To achieve a better match between the digital surface and the corresponding radiographs, a pose frame (aluminum structure) will be used to reference the posture (elbows) of the subject in both optical and radiological acquisition (Figure 6). The optical surface models will be evaluated together with the X-ray images at the ETH Zurich.

[figure not shown]

Figure 5: 3D optical digitalization with Artec EVA, <https://www.artec3d.com>

[figure not shown]

Figure 6: Pose-frame

## VI. Muscle fatigue

Muscle fatigue will be quantified using two parameters. First, the fatigue exercise duration will be measured using a stopwatch. Time is stopped from the point where the patients starts the exercise by no longer supporting the torso with their hands until the termination of the exercise by supporting the torso. Second, muscle fatigue will be assessed as the decrease in median EMG frequency as described by Boutellier et al. (2021) [31].

## VII. Radiological parameters

The measurement of *muscle atrophy* and *fatty infiltration* allows quantifying abdominal and paraspinal muscle degeneration. The analysis will be performed using ImageJ image analysis software (Version 1.52t, National Institutes of Health, Bethesda, Maryland) [32, 33].

For L1 to L5, we will measure the *cross-sectional area* (CSA) of the *abdominal and paraspinal muscles* on each side, including the multifidus and the erector spinae (longissimus and iliocostalis) muscles, and the CSA of the vertebral body. The relative CSA (rCSA) will be defined as the ratio between muscle CSA and vertebral body CSA and calculated for each level and side. The CSA of lean muscle in the region of interest will be defined as LeanCSA and measured on each side. The ratio of LeanCSA to the paraspinal muscle CSA will be defined as functional CSA (LeanCSA/CSA), represented as % muscle CSA and calculated for each level and side. Overall

CSA, rCSA and LeanCSA will be computed as average CSA (aCSA), average rCSA (arCSA) and average LeanCSA (aLeanCSA) across all levels considering the muscle as a single unit for each side [34]. In case a different validated (semi-) automated method for assessing muscle degeneration will become available during the study duration, such method will be applied. *Stenosis severity* will be classified according to Schizas [35]. *Segmental instability* will be determined as a relative shift in anteroposterior position of two adjacent segments between the upright standing radiograph and the lying MRI of more than 3mm [36].

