### **3. PROJECT POPULATION AND STUDY PROCEDURES**

#### **3.1 Project population, inclusion and exclusion criteria**

We plan to include 122 patients with sLSS (61 per year) in this study, which will be realistic and sufficient for the proposed statistical analysis (see Section 4.1). Patients will be recruited at the Department of Spine Surgery at the University Hospital Basel. The surgical procedure is not affected by the study and is not subject of investigation. All patients will receive – depending on their clinical and imaging diagnostics – lumbar decompression alone or decompression combined with fusion either through posterolateral fusion with pedicle screw-rod system with autologous bone apposition or through transforaminal lumbar interbody fusion with a cage filled with autologous bone implanted from posterolateral into the intervertebral space. Decompression will be performed as either open surgery or microsurgical technique, and both are performed through a midline approach. The open surgery decompression will be performed via an interspinous approach with interlaminar flavectomy, whereas in the microsurgical technique, uni- or bilateral fenestration and flavectomy will be performed.

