#### **XVI. Surgical information**

Information on the surgical procedure will be extracted from the patient files:

11. Scheduled decompression surgery
12. Scheduled fusion of vertebrae
13. Number of decompressed levels
14. Number of instrumented levels
15. In case of instrumentation:
  - Fusion with Cage
  - Fusion without Cage

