### 4.2. Statistical analysis plan

Baseline variables will be reported using mean and standard deviation, or median and interquartile range for continuous variables, and as counts and percentages for the categorical variables. Correlation analysis will be used for analysing the association between PROMs and continuous variables, including dynamic compensation, spinal imbalance, segmental instability, muscle degeneration and fatigue, and biomechanical parameters. For measuring the association between categorical variables (e.g., the severity of stenosis) and PROMs, we will perform an analysis of variance (ANOVA). Pre- to postoperative differences in PROMs, dynamic compensation, the severity of stenosis, spinal alignment, segmental instability, muscle degeneration, muscle fatigue, and biomechanical parameters will be assessed by comparing means using paired t-tests for continuous variables, and by comparing frequencies using the chi-square test for the categorical variables. Associations of pre- to postoperative changes in PROMs with changes in static and dynamic spinal imbalance, muscle fatigue, and extent of forwarding trunk bending and lumbopelvic range of motion during walking from before to after spinal stenosis operation will be assessed by computing the difference for each variable from before and after surgery for each patient and evaluating the correlation between these computed differences. The statistical methods described here assume the normal distribution of all parameters. In case of

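### The pre- to postoperative comparison of paraspinal muscle degeneration rests on L1–L5 averages that include the operated levels, and the listed data do not identify those levels

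*Protocol*

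**What the plan says.** **Measurement.** Protocol section 3.3 VII (Radiological parameters) opens its muscle measurements with "For L1 to L5, we will measure the" cross-sectional area of the abdominal and paraspinal muscles on each side. The paraspinal group includes the multifidus and erector spinae. Overall CSA, relative CSA and LeanCSA are then averaged "across all levels considering the muscle as a single unit for each side". Functional CSA (LeanCSA/CSA) is "represented as % muscle CSA and calculated for each level and side"; no all-level average is stated for it. Relative CSA also exists per level and side.

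**Timing and slices.** Section 3.3 (Study procedures) repeats the imaging at one year: "Because baseline and 1-year follow-up entail the same study procedures". On slice position it states that a "T2-weighted axial image will be selected at each vertebral body level in the center of the body itself".

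**Surgery between the visits.** Under section 3.1 all patients are decompressed through a midline approach, open or microsurgical. Some are also fused, by "posterolateral fusion with pedicle screw-rod system with autologous bone apposition" or by an interbody cage.

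**Surgical data.** Section 2.2 (Other parameters) and section 3.3 XVI list the count of decompressed levels, the "Number of instrumented levels" and cage use. Neither lists which levels were treated.

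**Analysis.** Section 4.2 sets out the comparison: "Pre- to postoperative differences in PROMs, dynamic compensation, the severity of stenosis, spinal alignment, segmental instability, muscle degeneration, muscle fatigue" and biomechanical parameters, with paired t-tests for continuous variables. It does not mention operated levels or type of surgery here, and it does not say which muscle index is tested.

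**The concern.** The multifidus and erector spinae lie beside a midline posterior approach. At an operated level, the muscle measured at one year has been through surgery as well as a year of ageing and disease. An average over all five levels merges two quantities: change in muscle that was left alone, and change in muscle at the surgical site.

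The share of the average that is affected differs between patients with the number of treated levels, so the surgical part is not a constant that could be subtracted. Analysing decompression and fusion separately would not remove it either, because every patient has at least one treated level.

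At stake is the reading of one secondary comparison. A fall in the average could be reported as progression of degeneration when part of it is a local effect of access or of altered image quality near implants.

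**Working it through.** The protocol gives no effect size, SD or power for change in muscle degeneration, so there is no planned figure to reproduce. The check has two parts.

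**1. Do the documents separate treated from untreated levels anywhere?**
- Definition (3.3 VII): all of L1–L5, with no distinction between visits or by operated level.
- Follow-up (3.3): the same procedures as at baseline.
- Data (2.2 and 3.3 XVI): counts of treated levels, not their identity.
- Test (4.2): paired, with no exclusion, stratification or adjustment for surgery.

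They do not. Per-level values would allow the separation, but only if the treated levels were known.

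**2. How far could a purely local effect move the average?**

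Assumptions (not in the protocol): equal muscle area at each level, an apparent local relative change *d* at *k* treated levels, and no change elsewhere. Then

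relative change in the five-level mean = *k* × *d* / 5.

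With *d* assumed at 10–30% loss:

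| Measured levels treated (*k*) | Share of average | Shift at 10% | Shift at 30% |
|---|---|---|---|
| 1 | 1/5 = 20% | 2% | 6% |
| 2 | 2/5 = 40% | 4% | 12% |
| 3 | 3/5 = 60% | 6% | 18% |

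A one-segment fusion instruments two vertebrae. S1 is not among the measured levels, so L5–S1 gives *k* = 1 and a segment between two measured vertebrae gives *k* = 2: a shift of 2–12%. A two-segment fusion gives *k* = 2 (L4–S1) or 3: a shift of 4–18%.

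**From patient to cohort.** These are shifts in one fused patient's average. If a share *f* of the cohort is fused, the implant-related shift in the cohort mean is *f* times the per-patient shift. The protocol gives no *f*. With *f* assumed at 25–50%, the one-segment range becomes 0.25 × 2% = 0.5% up to 0.50 × 12% = 6%, and the two-segment range 0.25 × 4% = 1% up to 0.50 × 18% = 9%. Any access effect in decompression-only patients would add to this; it is not quantified here.

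**Against what the test can detect.** 122 less 10% is 109.8, about 110 pairs. At two-sided 5% and 80% power a paired t-test detects (1.960 + 0.842)/√110 = 0.27 SD. Without an SD for the change, the percentage shifts cannot be put on that scale, so whether they would reach significance is unknown.

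**The case against.** Several counter-arguments have weight.

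- **The tested index is not named.** A reader might infer that section 4.2 tests the three all-level averages. It says only muscle degeneration. Functional CSA and relative CSA exist by level, and the choice of index for a secondary comparison can be left to an analysis plan. This stands as a limit. It does not dispose of the point: the averages are the only overall indices defined, and level-wise values can be sorted into treated and untreated only if level identity is known.
- **No hypothesis concerns this change.** Hypotheses 2.2 and 2.4 do not name muscle degeneration. It enters 2.1 and 2.3 as a morphological or severity factor and 2.5 as a preoperative one. This stands and limits the importance.
- **The mechanism is partly inferred.** The protocol does not discuss metal artefact, scarring or graft in the muscle bed, and it permits another validated measurement method. Slices lie at mid-vertebral body while decompression is interlaminar, so the effect in decompression-only patients may be smaller. Abdominal muscles lie outside the approach. All of this stands, and the local loss is therefore only an assumed range.
- **Treated levels could be recovered.** Surgical information comes from patient files, and follow-up images may show implants. A reader might infer that the information is lost; it probably is not. That makes the remedy cheap, but the protocol does not list the item.
- **Change at an operated level may be a real postoperative change.** Section 4.2 does not claim to isolate natural progression. This stands, and it argues against replacing the all-level average outright.

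**Conclusion.** The point holds for the paraspinal muscles in the pre- to postoperative comparison of section 4.2. Followed as written, the plan yields an all-level change that can mix degeneration with local surgical access and, by inference, implant effects on the images, and the listed data do not allow the two to be told apart.

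Per fused patient the size is 2–12% for one segment and 4–18% for two. This rests on an assumed local apparent loss of 10–30%, equal areas and no change elsewhere; the cohort mean shift is smaller and depends on an unstated fusion share.

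A reader might go further and infer that the study's main conclusions are compromised, or that a spurious significant result is to be expected. The documents support neither. The primary hypothesis concerns PROMs and dynamic compensation, the uses of muscle degeneration in Hypotheses 2.1, 2.3 and 2.5 are unaffected, and no SD is given from which to judge significance. The change should be made, but it concerns one secondary comparison.

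**What to change.** 1. In sections 2.2 and 3.3 XVI, extract from the patient files which levels were decompressed and which were instrumented, not only how many.
2. In section 4.2, name the muscle index compared before and after surgery. For paraspinal muscle, report the change separately for treated and untreated levels, using the same levels at both visits in each patient, beside the all-level average.
3. Base any statement about progression of degeneration on the untreated levels, and describe change at treated levels as postoperative change.
4. Keep the all-level average for the baseline analyses.

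The cost is one extra data item from a source already being used and one further averaging step; relative and functional CSA are already derived by level and side. The untreated-level average will be noisier and will draw on different levels in different patients. Patients with long constructs may have few or no untreated levels, so the number of patients and levels contributing should be reported with the result.
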